**Outcomes**			
Feasibility of Intervention Measure (FIM)	AAR Team Implementation Strategy Feasibility		✓
Acceptability of Intervention Measure (AIM)	AAR Team Implementation Strategy Acceptability		✓
Intervention Appropriateness Measure (IAM)	AAR Team Implementation Strategy Appropriateness		✓
Working Alliance Inventory-Short Revised (WAI-SR) Overall Score	CFT Clinical Intervention Fidelity Overall collaborative relationship	✓	✓
Parent Participation Engagement Measure (PPEM)	CFT Clinical Intervention Fidelity Collaboration and engagement	✓	✓
Collaboration & Satisfaction About Care Decisions (CSACD)—Satisfaction	CFT Clinical Intervention Outcome Satisfaction with decisions	✓	✓
SD County Behavioral Health Administrative Data	CFT Clinical Intervention Outcome Behavioral Health Service Linkage	✓	✓

Within team environments, shared mental models refer to the degree to which individual team members perceive key concepts (i.e., team, task) in a similar manner. For the CFT services intervention, shared mental models regarding perceptions of member roles, responsibilities, and goals can mediate more effective and efficient treatment planning. Team affect (i.e., trust and psychological safety) may also serve as mechanisms mediating success of the CFT services intervention. Psychological safety, a group-level phenomenon that correlates with team learning behaviors and performance, facilitates team members’ feelings of security [39] and focus on collective goals and problem prevention, rather than on self-protection [40–44]. Similarly, team trust is associated with decreased inefficiencies, greater negotiating effectiveness, and greater team effort, thus mediating overall team effectiveness [45–47]. Given the sensitivity and high stakes associated with CFT meetings (i.e., child placement, reunification), CFT members—particularly children/family—may feel uncomfortable fully participating for fear of negative repercussions. When CFT members experience enhanced shared mental models, psychological safety, and trust, they may be more open and willing to voice their opinions to collaborate on the treatment planning process for the CWS case.

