Immediately upon completion of each of the 5 CFT or CFT + AAR team meetings, the CWS caseworkers together with ~ 7 additional CFT members will provide data a via web-based online survey to assess mechanisms and outcomes. This results in 8 caseworkers leading 5 CFTs each for a total of 40 unique CFTs. Each of the 40 CFTs has ~8 participants, for a minimum total of 320 data points. See Fig. 2 for sampling.

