### Participants

There are four types of participants in this study. Participants will be (1) County CWS system leaders and caseworkers, (2) CFT informal and formal meeting members, (3) parents/caregivers with open CWS cases, and (4) children aged 6–17 with open CWS case. CWS caseworkers and CFT informal and formal support persons will be ≥ 18 years of age. Children and family members urrently open to CWS have a minimum age eligibility of 6 years to correspond with the CWS protocol for screening for behavioral health services need, and no maximum age limit for eligibility. Participants will be recruited from select regions, which will be determined in collaboration with CWS leadership prior to project implementation. Inclusion criteria for all groups of participants are intentionally broad to ensure valid analyses.

The research team will partner with County CWS to identify appropriate and representative CWS caseworkers to follow over the course of 5 CFT meetings. The 5 CFT meetings per CWS caseworker will be identified to best represent County CWS open cases. Additionally, only CFTs which include a child with an identified behavioral health services need will be included to optimize assessment of behavioral health services linkage. Behavioral health service need is determined by a preliminary administration of the Child & Adolescent Needs and Strengths (CANS) assessment by the CWS caseworker at the initial family visit. The CANS behavioral and emotional needs domain is employed for all children aged 6–17 as the screener for behavioral health services.

For children aged 6–17 open to CWS and with mental health services needs (identified via CANS screening and confirmed during initial CFT meeting perusual CWS), County Behavioral Health administrative data will be extracted to determine mental health service linkage. While children aged 6–17 may also participate in the CFT meeting, this is considered part of usual CWS services. No additional study participation from these children will be solicited. The proposed study will not apply any gender or minority exclusion criteria for participant selection. All efforts will be made to ensure that women and minority representation will be representative of County CWS.

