### Power analysis

Based upon the sampling strategy, power analysis was conducted to inform the detectable magnitude of effect. Power for the primary CFT services intervention outcomes, and team processes/emergent states outcomes, was estimated using a multi-step approach recommended by Hox [64]. First*,* a total number of observations was computed while ignoring nesting. With 8 team members from 8 child-family teams (4 per region) participating in data collection following each of 5 child-family team meetings, there is a total of 320 observation results. For these observations, the nested data structure introduces dependency that decreases the level of statistical power. To adjust for this, a second step was to penalize the total sample for nesting. This was accomplished using a reorganization of the design effect formula (i.e., *n*_*eff*_ = *n*/[1 + [*n*_*clus*_ − 1]*ρ*]), which provides the effective sample size of independent observations. Using conservative nesting effects for CFT members within CFT meetings, *ρ* = 0.20, the 320 observations provide statistical power equivalent to 36 independent observations. Third, the effective sample size was used to perform conventional, single-level power analysis using GPower. Assuming power of 0.80 and *α* = 0.05, results indicated that a small-to-medium main effect of *f*^2^ = 0.10 for condition on CFT clinical intervention outcomes may be detected. As noted, for the preliminary mediation tests, statistical power is necessarily limited. Simulations performed by Fritz and MacKinnon [65] have demonstrated that required sample sizes for mediated effects range from 35 to 74. This depends on the magnitude of the effects for the respective paths, with the smaller sample sufficient if both paths have large effects and the larger sample sufficient if both paths have medium effects. As such, the effective sample size of 36 is potentially sufficient if the magnitude of each effect for the respective paths is great.

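### The 80% power claim at f² = 0.10 extends to service linkage, a child-level outcome with about 40 values, for which power at that effect is about 50% or less

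*Protocol article*

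**What the plan says.** All references are to the protocol article.

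- **Power analysis, scope.** "Power for the primary CFT services intervention outcomes, and team processes/emergent states outcomes, was estimated using a multi-step approach". Linkage is not set apart, and the only caveat about limited power concerns the mediation tests.
- **Power analysis, base.** Eight members, eight teams and five meetings are multiplied: "there is a total of 320 observation results". With ρ = 0.20 for members within meetings, these are reduced to 36 effective observations.
- **Power analysis, claim.** At 80% power and α = 0.05, an effect of f² = 0.10 "for condition on CFT clinical intervention outcomes may be detected".
- **Table 1, Outcomes.** The clinical intervention outcome label is attached to two rows: CSACD satisfaction, and "CFT Clinical Intervention Outcome Behavioral Health Service Linkage".
- **Participants.** For children with an identified need, "County Behavioral Health administrative data will be extracted to determine mental health service linkage". No other study participation is sought from the children.
- **Specific aim 3.** "This results in 8 caseworkers leading 5 CFTs each for a total of 40 unique CFTs". Four caseworkers are assigned to each arm. The Fig. 2 note and the Power analysis instead describe 8 teams, each measured at 5 meetings.

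**The concern.** A power statement holds only for outcomes that share its unit, sample size and correlation structure. This one is built from survey ratings by about eight people per meeting. Linkage is not rated by anyone: it is read from the child's administrative record, and any correlation that matters for it lies between children of the same caseworker, a level at which the article gives no value. The claim nevertheless covers linkage by its label.

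Linkage is the last step of the article's mechanistic model, the stated reason for restricting entry to CFTs with an identified need, and the one outcome in Table 1 not taken from participant ratings. If 80% power at a small-to-medium effect is taken at face value, a non-significant linkage result could be read as evidence against such an effect, when the trial is about as likely to miss it as to find it, or more likely.

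**Working it through.** **Inputs from the article.** α = 0.05 (taken as two-sided; sidedness is not stated); target power 0.80; f² = 0.10; 320 ratings; ρ = 0.20; effective n 36; 40 CFTs; 8 caseworkers, 4 per arm, 5 CFTs each.

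**Assumptions of this check.** One index child per CFT, so 20 children per arm. Linkage treated as yes/no where proportions are used; the article does not define the variable. Caseworker ICC 0, 0.05, 0.10 or 0.20. Control linkage rate 30%, 50% or 60%. None of these is given.

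**1. The plan's own figures.** n_eff = n/[1 + (n_clus − 1)ρ].
- n_clus = 40: 320/(1 + 39 × 0.20) = 320/8.8 = 36.4. This reproduces the stated 36.
- n_clus = 8, the members per meeting: 320/(1 + 7 × 0.20) = 320/2.4 = 133.3.

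Power comes from the noncentral F distribution with one predictor, N − 2 denominator degrees of freedom and noncentrality f² × N. At N = 36, power at f² = 0.10 is 45%, and the f² detectable at 80% is 0.23. One-sided, these are 58% and 0.18. An effect of f² = 0.10 needs N of about 81 (64 one-sided). The stated f² = 0.10 is therefore not reproduced at n = 36 for any outcome.

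**2. Linkage, independent children.** N = 40.
- Noncentral F: power at f² = 0.10 is 50%; f² detectable at 80% is 0.21.
- As proportions: phi² = f²/(1 + f²) = 0.10/1.10 = 0.091, so phi = 0.30, for example 35% v 65%. The two-proportion normal approximation with 20 per arm gives 47%, and Fisher's exact test 34%.

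**3. Linkage, children clustered by caseworker.** n_eff = 40/(1 + 4 × ICC), then the same noncentral F.

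| Assumed ICC | n_eff | Power at f² = 0.10 | f² detectable at 80% |
|---|---|---|---|
| 0 | 40 | 50% | 0.21 |
| 0.05 | 33.3 | 42% | 0.25 |
| 0.10 | 28.6 | 37% | 0.30 |
| 0.20 | 22.2 | 29% | 0.39 |

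**4. Difference in linkage detectable at 80% power** (two-proportion normal approximation, 20 per arm, no clustering): 30% to 73%, 50% to 90%, 60% to 96%. With clustering the differences grow; against a 30% control rate the treated rate must reach 77%, 80% or 86% at ICC 0.05, 0.10 or 0.20.

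**5. Precision, 60% v 80%.** SE = √[(0.6 × 0.4 + 0.8 × 0.2)/20] = √0.02 = 0.141. At ICC 0.20, SE = 0.141 × √1.8 = 0.190. If the interval is based on eight caseworker proportions, there are 6 degrees of freedom and t = 2.447, so the half-width is 2.447 × 0.141 = 35 points, or 2.447 × 0.190 = 46 points. A normal quantile would give 28 and 37, too narrow for that analysis.

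**6. The other team count.** If there are 8 teams each met five times, as the Fig. 2 note and the Power analysis have it, there would be about 8 children and far less power.

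**The case against.** The strongest objection is that the unit of analysis does not explain most of the shortfall. The article does not compute power on 320; it uses 36, which is already below 40. Independent children would give slightly more power at f² = 0.10 (50%) than the plan's own base (45%). This stands: much of the gap is the separate failure of f² = 0.10 to follow from n = 36. A reader might infer that counting ratings instead of children by itself turned 80% into 50%; the article's figures do not support that. The linkage point still does not disappear once the other error is corrected. If the effective n were recomputed with eight members per meeting, it would be 133 and the survey scales would have 95% power at f² = 0.10, while linkage would stay at about 50% or less.

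It can also be said that the outcome label is used loosely, since the same block of Table 1 lists fidelity measures, and that the survey basis is visible in the text. But the label matches two rows exactly, linkage is one of them, and no exception is made.

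Finally, Aim 3 is described as a pilot test and linkage is not named as the single primary outcome. Both are true and limit the weight of the point. They do not make an explicit 80% statement correct.

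**Conclusion.** The power statement is wrong as written for linkage. Its construction does not describe a child-level administrative outcome, and at the stated effect the power is about 47–50% with 40 independent children and about 42%, 37% or 29% at an assumed caseworker ICC of 0.05, 0.10 or 0.20. The detectable f² is about 0.21, rising to about 0.39 over that range.

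The child-level source is stated in the article. One child per CFT and the ICC range are assumed, and the yes/no form is inferred. The noncentral F results do not depend on the yes/no form. The ρ of 0.20 in the article is for members within meetings; using 0.20 for children within caseworkers is an assumption of this check.

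A reader might infer that the trial could detect only a near-maximal effect on linkage. That goes too far: without clustering, 30% v 73% is detectable, which is very large but not near the ceiling. The description fits only higher control rates or marked clustering, and the article gives neither figure. Its background statement on foster youth without services concerns receipt over 12 months, not linkage after a CFT, and does not settle the control rate.

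**What to change.** In the Power analysis section:

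1. Do not apply the member-level detectable effect to linkage.
2. Do not keep f² = 0.10 for the survey outcomes either without recomputing it from the effective n that is finally adopted; at 36 it is 0.23.
3. Add a separate line for linkage: about 40 children, 20 per arm and 5 per caseworker; the assumed caseworker ICC range; and the detectable difference at 80% power over assumed control rates (unclustered 30% to 73%, 50% to 90%, 60% to 96%, larger with clustering).
4. State that a non-significant linkage result will be reported with its confidence interval and not read as no effect. If the interval is based on caseworker-level proportions, quote half-widths on 6 degrees of freedom: about 35 points (ICC 0) to 46 points (ICC 0.20) for 60% v 80%.
5. Reconcile the 40 CFTs in Specific aim 3 with the 8 teams in the Fig. 2 note and the Power analysis, because the number of linkage values depends on it.

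The cost is wording. No extra participants are needed. The stated figure for linkage becomes less favourable, as does the survey figure if the effective n stays at 36.

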### Dissemination plan

Beyond plans to submit data elements to ClinicalTrials.gov, aggregate data will be synthesized and summative feedback of the findings and areas that warrant further attention will be provided to CWS. This will provide practically relevant and actionable data to inform policy and practice implementation locally. Additionally, study findings will be prepared and submitted for publication in peer-reviewed scientific journals. All peer-reviewed scholarly publications will be submitted to the National Center for Biotechnology Information and PubMed Central at the US National Institutes of Health’s National Library of Medicine.

## Discussion

Effective CWS practice relies on the role of child protection caseworker in partnering with children and families to create a service Action Plan directed towards family strengths and needs. This study responds to the critical importance of including families in decision-making processes, which facilitates engagement in the Action Plan, promoting use of needed behavioral health services. This study has the potential to demonstrate the feasibility and utility of the AAR to enhance CFT implementation and effectiveness.

As with any research study, the potential for operational issues is present and may serve as a challenge to performing the study. The COVID-19 pandemic has intensified disparities for several communities [66]. In the event that CFT meetings have not resumed in person, the research team may encounter related practical challenges through the use of a virtual meeting platform. Given that communities may have unequal access to virtual resources [66], including cell phones and laptops to stay engaged with services, there may be a limited range of sample that lacks economic and/or racial diversity. In addition to resource inequity and restricted range of sample, there could be additional, unanticipated technological barriers when conducting the AAR team effectiveness intervention following the virtual CFT meetings.

The research team remains sensitive to the potential coercion of parent/caregiver—an issue that is discussed often in the context of CWS participation for which parents/caregivers may feel obligated to “demonstrate cooperation [67]”. To the best of the ability of the research team, this concern for potential coercion as specifically related to the research is mitigated by several intentional considerations. First, the informed consent process will be conducted by a member of the research team who has completed a training in cultural competence in research and evaluation. Then, the informed consent process itself includes multiple components. Introductions to the relevant individuals will clearly identify the researchers, who will define the purpose and nature of the study and ensure that parent/caregiver understands the scope of what is being asked of them. Prospective parent/caregiver will have an opportunity to ask questions before deciding to participate. Objectives will be made clear. An honest assessment of the risks or potential adverse impacts of the research, which should be minimal for these participants, will be provided. Potential usefulness of the research for the child-welfare involved children and parents/caregivers in general will also be explained. Privacy and confidentiality will be addressed throughout the study.

The research team, and all consent forms, will underscore that enrollment and continued participation are completely voluntary. And, of utmost importance, the research team will ensure that potential participants fully understand that their declination to participate in the research component will in no way negatively impact the services that they or their children will receive as part of their child welfare involvement. Parents/caregivers may terminate participation at any time if they become uncomfortable with the research study. Participants will be provided with investigator contact information if they wish to discuss concerns about discomfort. Also, prior to enrolling any participant, a clear understanding will be documented from CWS administration that the study will not be able to share any individual data with CWS, and that no individual’s study data will be used for CWS-related service provision. As an additional safeguard against coercion, CWS caseworkers will be naïve to whether parents/caregivers consent or decline research participation.

This project has the potential to benefit service delivery and integration for CWS leaders, caseworkers, formal and informal CFT member support persons, parents/caregivers, and children with open cases. By inclusion of child and family voice, the AAR-enhanced CFT should lead to increased fidelity to the CFT intervention and greater levels of parental satisfaction and shared decision-making, thus resulting in enhanced follow-through with service plans and linkage to mental health treatment services for children. Improving intervention effectiveness, both at the system and family levels, is crucial for practice efficiencies and improved child and family outcomes.

## Data Availability

N/A.
